#### Data Analysis

Demographic characteristics pre- and postimplementation for each hospital will be described using medians with IQRs, means with SDs, and frequencies with percentages, as appropriate. The primary outcome will be compared within each hospital pre- and postimplementation using separate logistic regression models for each hospital, with adjustment for the following patient characteristics: age, sex, reason for ICU admission, status on ICU admission (ie, Charlson Comorbidity Index, APACHE II, GCS, and SOFA), therapies received while in ICU (ie, ventilation, vasoactive medications, intermittent hemodialysis, and continuous renal replacement therapy), status on transfer (ie, transfer delay time, transfer decision cancellations, and ICU occupancy), and ICU length of stay. Pooled analyses across all four hospitals will use mixed-effects logistic regression models with a fixed effect for intervention and a fixed effect for time in months, in order to model the underlying secular trend. A fixed effect for patient characteristics will also be used, as noted above, and random effects will be used for hospital and hospital by time to account for intracluster and interperiod correlation. In case of poor model fit or convergence issues due to a limited number of clusters, hospital-level analyses will be considered by aggregating the primary outcome over all summaries in each hospital during each month and using linear regression of the aggregated cluster-period proportions of complete and timely summaries with fixed effects for hospital and time in months. Secondary outcomes will be analyzed as described for the primary outcome, using within-hospital and pooled analyses. Wilcoxon rank-sum tests will be used to compare ICU and hospital length of stay, and log-rank tests will be used to compare time from ICU discharge to hospital mortality.

Open-ended comments collected through clinician surveys will be analyzed according to standard practices of qualitative textual analysis.

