### Study Design

This study uses a cluster-specific pre-post trial design with randomized and staggered implementation of the e-transfer tool across four hospitals.

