### E-Transfer Tool Implementation

The e-transfer tool has been sequentially implemented into the four study hospitals at a new site every 2 months. This occurred between July 2018 and January 2019. The study biostatistician (AS), who was not involved with clinical practice in the ICUs, randomized the order of hospitals for implementation. Dictation remained available after implementation, but the ICU e-transfer tool was endorsed as the primary method to prepare ICU transfer summaries; as well, use of the tool was supported with strategies that have been successfully used in previous local initiatives, including in-person and web-based education, point-of-care support, and electronic audit and feedback [50].

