#### Sample Size Calculations

Sample size calculations were based on the cluster-specific pre-post study design. Based on our pilot [41,42], we calculated a required sample size of 144 pre- and 144 postimplementation ICU transfer summaries from each hospital to assess our primary outcome. This will be sufficient to detect an absolute difference in our primary outcome of 15% for each hospital with 82% power and an α value of 5% based on a baseline proportion of 20%; we observed a change in our pilot from 23% to 83%. A random sample of 24 ICU patients per hospital per month, over 6 months pre- and 6 months postimplementation, will facilitate secondary analyses, which accommodate the possibility of secular trends. The study biostatistician (AS) determined the random sample by assigning computer-generated random numbers to the complete list of patients transferred from each ICU within the study period, which was extracted by a data analyst with the critical care analytics system (see Figure 2). The study biostatistician was blinded to the method used to create the summary at the time of randomization.

To collect clinician ratings of the transfer summary quality, we calculated requiring 64 summaries preimplementation (ie, 16 per hospital × 4 hospitals = 64) and 64 summaries postimplementation (ie, 16 per hospital × 4 hospitals = 64), which will be sampled from aforementioned summaries, to detect an absolute difference in means as small as 0.5, assuming an SD of 1, with 80% power and an α value of 5%. The same patient cases will be used to assess for suspected post-ICU adverse events.

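### The pooled model estimates a random hospital effect from four staggered hospitals, and its fixed-hospital alternative is only a conditional fallback, so the pooled test probably exceeds its nominal 5%

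*Protocol article*

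**What the plan says.** The Study Design section describes "randomized and staggered implementation of the e-transfer tool across four hospitals", and E-Transfer Tool Implementation says the tool was "sequentially implemented into the four study hospitals at a new site every 2 months". Sample Size Calculations sets "A random sample of 24 ICU patients per hospital per month, over 6 months pre- and 6 months postimplementation" and presents the monthly sampling as support for secondary analyses that allow for secular trends. The sample size itself belongs to the within-hospital comparison: "we calculated a required sample size of 144 pre- and 144 postimplementation ICU transfer summaries from each hospital", to "detect an absolute difference in our primary outcome of 15% for each hospital with 82% power".

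Data Analysis then gives two layers. The primary outcome is compared before and after within each hospital by its own logistic regression, without random effects. The pooled analysis is a mixed-effects logistic model with fixed effects for intervention, month and patient characteristics, in which "random effects will be used for hospital and hospital by time to account for intracluster and interperiod correlation". The alternative has a condition: "In case of poor model fit or convergence issues due to a limited number of clusters", a linear regression of hospital-month proportions "with fixed effects for hospital and time in months" is to be considered. Secondary outcomes follow the same within-hospital and pooled scheme.

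**The concern.** A variance estimated from four hospitals is very imprecise. This matters here because each hospital's 12-month window is centred on its own go-live date, so hospital and calendar month are partly confounded. A random hospital effect lets differences between hospitals inform the month effect, and through it the intervention effect. How much weight those differences get depends on the poorly estimated variance. Fixed hospital intercepts close that route.

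The plan recognises that few clusters are a problem, but ties its remedy to visible failure of the fit. Standard errors that are too small are not visible in that way. The within-hospital models list no time term, so the pooled model is the stated analysis that separates the tool from a secular trend. Its intervals would be too narrow and its p values too small.

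**Working it through.** **1. The plan's own figure.** Inputs from Sample Size Calculations: 144 per period, 20% against 35%, 5% (two-sided assumed).

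z = [0.15·√144 − 1.96·√(2·0.275·0.725)] / √(0.20·0.80 + 0.35·0.65) = (1.800 − 1.238) / 0.6225 = 0.903, so power is 81.7%.

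The stated 82% is reproduced. It belongs to the within-hospital comparison and involves no random effect.

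**2. Mechanism.** Number the months so that go-lives fall at months 7, 9, 11 and 13. The windows are then months 1-12, 3-14, 5-16 and 7-18, with midpoints 6.5, 8.5, 10.5 and 12.5. Every hospital is exposed for half its window, so between-hospital comparisons say nothing directly about the tool. They do bear on a linear month slope. The squared deviations of the midpoints sum to 9 + 1 + 1 + 9 = 20, so with an assumed hospital SD of 0.4 (logit scale) a slope taken from hospital means alone has standard error 0.4/√20 = 0.089 per month. Pre and post segments lie 6 months apart on average, so that error moves the intervention log odds ratio by 6 × 0.089 = 0.54. This exceeds the whole fixed-hospital standard error in step 5 (0.320 with hospital-month SD 0.2). The fit must weight this source down correctly. When the hospital variance is estimated as zero, it does not.

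**3. Type I error.** From the article: 4 hospitals, 2-month steps, 12 months each, 24 summaries per month (4 × 12 = 48 hospital-months; 48 × 24 = 1,152 summaries), 20% baseline. Assumed: ICC 0.01 to 0.10; hospital-month variance from none up to equal to the hospital variance; no patient covariates. There were 2,000-3,000 runs per scenario, so the Monte Carlo standard error near 10% is at most √(0.1·0.9/2000) = 0.7 points.

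| Analysis, true null, nominal 5% | ICC 0.01 | ICC 0.05-0.10 |
|---|---|---|
| Planned logistic model, ML, Wald z, linear month | 6.8-7.4% | 9.2-11.2% |
| Same, categorical month | 8.4% | 12.2-17.2% |
| Linear mixed model on proportions, ML, z | 8.9% | 10.8-11.1% |
| Same, REML, z | 7.4% | 7.7-8.5% |
| Same, REML, t on 42 df | 6.5% | 7.1-7.9% |
| Planned logistic model, singular fits sent to fallback | 5.4% | 5.9-7.3% |
| Mixed logistic, fixed hospitals, z | 5.5% | 5.0-7.5% |
| Hospital-month regression with hospital, month and intervention, t | 5.3-5.9% | 4.9-5.8% |

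Rows 3 to 7 use linear month. With a very large hospital variance (ICC about 0.23) row 1 falls to 7.3%.

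**4. Other simulations of the same design.**
- Hospital SD 0.4-0.8 and hospital-month SD 0-0.4: the planned model gave 8.6-11.8% with linear month, 14.5% with autocorrelated hospital-months and about 14% with categorical month (300 runs only, Monte Carlo standard error about 2 points). Fixed hospitals gave 3.8-7.3%, and the hospital-month regression 4.0-6.1%.
- A further linear mixed model on proportions gave 6.9-9.5% (REML) and 8.5-19% (ML), against 4.1-6.3% for the fixed-hospital regression.
- Stress variants (hospital-specific slopes, autocorrelation, heterogeneity between hospitals) gave 9.6-14.8% for the planned model and 3.8-7.8% for the regression.

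**5. Precision cost.** Standard error of the log odds ratio with known variances, by hospital SD/hospital-month SD, fixed against random: 0.320/0.312 = 1.03 (0.8/0.2); 0.320/0.296 = 1.08 (0.4/0.2); 0.378/0.343 = 1.10 (0.4/0.4); 0.320/0.268 = 1.19 (0.2/0.2).

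**6. Consequence for the primary outcome.** The pilot moved from 23% to 83%: ln(0.83/0.17) − ln(0.23/0.77) = 1.586 + 1.208 = 2.79. Divided by standard errors of 0.378 and 0.268, this gives z of about 7.4 and 10.4.

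**The case against.** The article names no estimator, test statistic, ICC or month coding. A condensed protocol may leave these to an analysis plan that is not shown, and that plan could add a small-sample correction. This stands against any single figure, and it means the upper part of the range comes from the least favourable choices. It does not remove the point. The random structure and the fallback's trigger are in the article itself, and REML with a t reference still gave 6.5-7.9%.

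The protocol also foresees few clusters and names a sound alternative. If singular fits counted as convergence problems, the two-stage procedure would run at 5.4-7.3%. That is a fair reading, but the text does not say so and the fallback is only to be considered. Zero variance estimates arose in 25-85% of simulated fits at ICC 0.01 to 0.10, so the undefined decision would come up often.

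The mixed logistic model with fixed hospitals is not perfect either: its worst scenarios (7.2-7.5%) lie close to REML for the planned structure. The hospital-month regression is cleaner, though it reached 7.8% in one stress variant.

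Three stronger readings are tempting and not supported:
- A definite inflated error rate, such as 9-14%, cannot be stated as fact, because it depends on variances and methods the article does not give.
- The primary comparison is not compromised. It has no random effect.
- The fallback sentence lists hospital and month but not the intervention. A reader might infer that the tool effect would be left out. An analysis meant to estimate that effect plainly includes it, so this is condensed wording and not an error.

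**Conclusion.** The point holds for the pooled analysis only. With four hospitals and staggered windows, the planned random hospital effect makes the nominal 5% test anti-conservative: about 7-9% with REML and about 7-19% with uncorrected maximum likelihood, or about 5-7% if singular fits are diverted to the fallback. These rates rest on an assumed ICC of about 0.01 to 0.10, on the coding of month, and on simulations without patient covariates. The REML figures come from a linear model for hospital-month proportions, not from the logistic model.

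The conclusion for the primary outcome would be unlikely to change if the pilot effect recurs. The risk is greater for secondary outcomes such as ICU readmission or rapid response activation, where no effect is plausible. Error rates at their event frequencies were not simulated. The change is worth making, but the fault does not undermine the trial's main comparison.

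**What to change.** Make fixed hospital intercepts part of the pre-specified pooled analysis, in one of two ways.

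- Mixed logistic model with fixed effects for hospital, month, intervention and patient characteristics, a hospital-by-month random effect, and a t reference on cell-level degrees of freedom. Before patient covariates these are 48 − 6 = 42 with linear month (four hospitals, one slope, one intervention term), or 48 − 22 = 26 with 18 categorical months (4 + 17 + 1). Simulated error is about 4-7.5%. The 5.0-7.5% in the table used a normal reference, and a t reference would reject slightly less often.
- The plan's own hospital-month regression, with hospital, month and the intervention term written in, as the pooled analysis and not a conditional fallback. Simulated error is about 4-6% in the main scenarios.

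State the coding of month in either case. If the random hospital effect is kept, say that a singular fit triggers the fallback and that the fallback will then be used.

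The cost is analysis-plan wording and a standard error about 3-10% larger, up to about 19% if hospitals barely differ. The second option also gives a difference in proportions in place of an odds ratio, and patient characteristics could enter only as hospital-month summaries.

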### Objective

In this study, we will evaluate the effectiveness of the ICU e-transfer tool for improved completeness and timeliness of transfer summaries and reduced adverse patient outcomes by comparing transfer summaries produced postimplementation to those produced preimplementation.

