**Transfer summary quality**		
	Overall completeness: proportion of eight requisite information elements present in transfer summary (%) and presence or absence of each essential information element in transfer summary	Summative score of the presence (score=1) of eight essential information elements—the four elements listed above and the following elements: Patient medical history Patient supportive needs (ie, venous thromboembolism prophylaxis, isolation, mobility, or nutrition) Patient attachments (ie, lines and tubes) Medication reconciliation
	Timeliness: availability of summary relative to the date and time of patient transfer (in hours)	Difference between the following: Date and time transfer summary was transcribed (ie, dictated summaries) or last edited (ie, electronic summaries) and Date and time of patient transfer from ICU
	Clinician ratings: clinician ratings of perceived general quality of transfer summary (median, IQR)	Rate five criteria on a 7-point Likert scale: Organization Completeness Pertinence Overall satisfaction Confidence that accepting team will understand patient care plan

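### The 15-covariate primary model is carried into within-hospital analyses of adverse events, where each hospital has only 32 assessed patients

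*Protocol article*

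**What the plan says.** The Data Analysis section of the protocol article compares the primary outcome before and after implementation "using separate logistic regression models for each hospital, with adjustment for the following patient characteristics: age, sex, reason for ICU admission". The list then adds four measures of how ill the patient was on arrival (the Charlson index and the APACHE II, GCS and SOFA scores) and four organ-support treatments. It ends with "status on transfer (ie, transfer delay time, transfer decision cancellations, and ICU occupancy), and ICU length of stay". A pooled mixed-effects logistic model follows, with the same patient characteristics, a fixed effect for time in months, and random effects for hospital and hospital by time. If the model fits badly or fails to converge because there are few hospitals, monthly hospital proportions of the primary outcome may be analysed by linear regression instead.

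For the rest, the section states: "Secondary outcomes will be analyzed as described for the primary outcome, using within-hospital and pooled analyses". The next sentence gives length of stay a rank-sum test and time to hospital death a log-rank test. No other secondary outcome has a method of its own.

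The Sample Size Calculations section derives 64 summaries per period (16 per hospital) for the clinician ratings and adds: "The same patient cases will be used to assess for suspected post-ICU adverse events". The Objective section includes "reduced adverse patient outcomes by comparing transfer summaries produced postimplementation to those produced preimplementation" among what the study will evaluate.

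**The concern.** The adjustment set was chosen for an outcome with 288 sampled summaries per hospital. The blanket sentence carries it to an outcome observed in one ninth as many patients (32 of 288). A logistic model with about as many parameters as events will usually separate: some combination of covariates predicts the outcome perfectly, so at least one estimate is infinite. Software then stops, or prints huge odds ratios with meaningless intervals.

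Two things are at stake. First, if the stated model fails, its replacement is chosen after the data are seen, for the outcome that carries the patient-safety part of the objective. Second, the adverse-event sample was sized for ratings, so a comparison without a significant difference says little about whether harm changed.

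**Working it through.** **Plan's own figures.** For 144 vs 144, 20% vs 35%, two-sided 5% (sidedness assumed), power is Φ{(|p1−p2|√n − 1.96√(2p̄(1−p̄))) / √(p1(1−p1)+p2(1−p2))}. This gives Φ{(0.15×12 − 1.96×0.631)/0.622} = Φ(0.903) = 81.7%, against the stated 82%. For ratings, n = 2(1.96+0.842)²×1²/0.5² = 63 per period, against the stated 64. Both reproduce.

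**Parameter count.** Age, sex and reason for admission (3); admission status (4); ICU therapies (4); transfer status (3); ICU length of stay (1). The total is 15. Adding the period term gives 16 slopes, and the intercept makes 17 parameters. The count is higher if reason for admission has more than two categories.

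**Adverse events within one hospital, n = 16 + 16 = 32.** The documents give no rate, so a range is assumed. Events = 32 × rate; events per slope = events/16. Separation was checked by linear programming on simulated data with no true effects and one slope for reason for admission.

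| Assumed rate | Events | Events per slope | No finite estimate: simulation A | Simulation B |
|---|---|---|---|---|
| 10% | 3.2 | 0.2 | 100% | 100% |
| 20% | 6.4 | 0.4 | 98% | 96% |
| 30% | 9.6 | 0.6 | 94% | 81% |
| 50% | 16 | 1.0 | 88% | 65% |

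The two simulations differ in the assumed covariate distributions; A includes some uncommon binary covariates. For comparison, the primary outcome has 144×0.20 + 144×0.35 = 79 events per hospital, or 79/16 = 5.0 per slope.

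**Adverse events pooled, n = 128.** With all 15 covariates, period and one time term (17 slopes), assumed rates of 10/20/30% give 12.8/25.6/38.4 events, or 0.8/1.5/2.3 per slope. Separation occurred in 64/23/6% of datasets with a similar 16-slope design. A model with intervention, three hospital contrasts, one linear time term and one severity score has 6 slopes, or 2.1/4.3/6.4 events per slope.

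**Other 3-day events, if analysed on 288 per hospital.** Neither the rates nor this denominator is stated. With uncommon binary covariates, separation occurred in 99/93/59/31% of datasets at assumed rates of 1/2/5/8%. With binary covariates at 35% prevalence it was 91% at 1% but only 3% at 5%.

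**What 64 vs 64 can show.** For a one-third fall from an assumed 20% (to 13.3%), unadjusted: Φ{(0.0667×8 − 1.96×0.527)/0.525} = Φ(−0.952) = 17%. For 80% power the rate would have to fall from 20% to about 4%: Φ{(0.16×8 − 1.96×0.460)/0.445} = Φ(0.851) = 80%.

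**Price of the time term.** Number the 12 sampled months of a hospital 1 to 12. The pre and post means are 3.5 and 9.5, so the between-period variance is 3² = 9. The total variance is (144−1)/12 = 11.92. With hospital effects and a linear month term, 9/11.92 = 75.5% of the variation in time is shared with the intervention. The variance of its estimate rises by about 1/(1−0.755) = 4.1, and its standard error about doubles. The 17% is therefore optimistic for a time-adjusted comparison.

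**The case against.** Several stronger readings are tempting, and the documents do not support them.

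- **That every secondary outcome gets the primary model.** It does not: length of stay and time to death have their own tests.
- **That hours and ratings will be forced into a binary model.** The sentence can equally mean the same within-hospital and pooled structure with the same adjustment. Ratings are sized on a difference in means, so the authors do not treat them as binary. A full analysis plan may name each model. Because timeliness is defined as "availability of summary relative to the date and time of patient transfer (in hours"), a clarifying phrase is useful, but this is not an error.
- **That models for readmission, rapid response activation and cardiac arrest cannot be fitted.** This rests on rates the documents do not give. These events are extracted electronically, and nothing limits them to the 288 sampled patients. At 5%, separation ranged from 3% to 59% depending on the assumed covariates.
- **That the primary analysis is compromised.** About five events per slope is modest but workable, and nothing here changes it.

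It is also fair to say that a pooled analysis is already planned, that the subsample was sized as a pooled total, and that the article claims no power for adverse events. This makes the consequence smaller but does not rescue the within-hospital model, which the sentence explicitly requires. Nor does the fallback, which is written for the primary outcome and for too few hospitals. The conflict lies between two statements in the article, so an unseen analysis plan does not explain it away.

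**Conclusion.** The point stands in a narrow form. The stated within-hospital adverse-event model, with at least 17 parameters for 32 patients, has no finite estimate in most datasets at any assumed rate from 10% to 50% (about 65% to 100%, depending on rate and covariate distribution). Those rates and distributions are assumptions; the parameter and patient counts come from the article. The same failure reaches other 3-day events within a hospital only at about 1% to 2% or less of an assumed 288 patients. The full 15-covariate model is also thin when adverse events are pooled. This is a should-fix matter: it concerns a secondary outcome, and the primary comparison is untouched.

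**What to change.** Replace the blanket sentence with rules by outcome:

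1. **Adverse events.** Per hospital, report counts and proportions with confidence intervals, without a model. Compare the periods in the pooled data only, by penalised (for example Firth) logistic regression with intervention, hospital, time in months and one severity score named in advance. The time term must stay, because the plan includes it for the secular trend and without it the intervention effect is confounded with calendar time.
2. **Other 3-day events.** Apply the same rule wherever there are too few events for the 15-covariate model. Fix the threshold in advance and state the denominator.
3. **Interpretation.** Describe the 64 vs 64 adverse-event comparison as estimation with a confidence interval, and word the objective to match.
4. **Clarification.** State that timeliness in hours, the 0–8 completeness score and the 7-point ratings keep the within-hospital and pooled structure but use models suited to their scale.

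The cost is a few sentences and no new data. The downside is less covariate adjustment for sparse outcomes. The reduced model also omits the hospital-by-time random effect, which could hardly be estimated from 128 patients over 4×12 = 48 hospital-months (2.7 per cell). Intervals will be wide, partly because of the time term.
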